### Outcome

Women will be followed-up for the incidence of type 2 diabetes. The incident onset of type 2 DM will be ascertained using a validated definition [34]. That algorithm requires one hospital record including a diabetes-specific International Classification of Disease code (ICD) OR two physician claim records relating to diabetes treatment within 1 year of each other, OR a dispensing record for an anti-diabetic drug from the Ontario Drug Benefit. According to this definition, diabetes records occurring between 120 days before or 180 after a hospital or primary care record of pregnancy care are considered to relate to gestational diabetes and are excluded.

Where physician claim records are used to ascertain DM status, DM diagnosis date is set to the date of the first visit. The validated definition has a sensitivity of 90.0%, a specificity of 97.7%, and a positive predictive value of 82.6%. Women will be followed up from index date until the earliest of incident diabetes, death, new pregnancy conception date, or study end-date (31st March 2019).

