To obtain outcome data, we will use the Ontario Diabetes Database (ODD). This database was established in 1991 and contains all individuals with DM in Ontario. This database captures data from hospital discharge abstracts, Ontario drug benefit claims and physician service claims and data from this database are currently available until 31st March 2019. The use of data in this project was authorized under section 45 of Ontario’s Personal Health Information Protection Act, which does not require review by a Research Ethics Board.

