### Participants

The derivation cohort will consist of all women aged between 16 and 50 years (at index pregnancy) whose pregnancy resulted in a live birth or still birth in Ontario between 1st April 2006 and 31st March 2014. No minimum duration of pregnancy was required for inclusion into the derivation cohort. For women who had multiple pregnancies during this period, the first pregnancy occurring during the accrual window will be selected. The influence of this choice of pregnancy will be examined in sensitivity analyses involving the development and validation of models in separate cohorts containing a randomized choice of pregnancy. Women with pre-pregnancy DM as ascertained using the ODD and available variables in BORN indicating pre-existing DM will be excluded from the derivation cohort. Women who were ineligible for the Ontario Health Insurance Plan or were a non-Ontario resident in the 2 years prior to index date will be excluded since predictor and outcome data for these women will be incomplete. Index date is defined as 6 months post-partum. Women who had a second pregnancy prior to the index date and women who died prior to index will also be excluded.

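### Follow-up and outcome data both end on 31 March 2019, so diabetes found by two claims is under-counted when the first physician claim falls in the preceding year

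*Protocol article*

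**What the plan says.** Methods, Data sources, says of the Ontario Diabetes Database that "data from this database are currently available until 31st March 2019". Methods, Outcome, follows women from the index date "until the earliest of incident diabetes, death, new pregnancy conception date, or study end-date (31st March 2019".

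Outcome gives three routes to a diagnosis. Two need a single record: a coded hospital record, or "a dispensing record for an anti-diabetic drug from the Ontario Drug Benefit". The third needs "two physician claim records relating to diabetes treatment within 1 year of each other", and for that route "DM diagnosis date is set to the date of the first visit".

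Participants defines the cohort by "live birth or still birth in Ontario between 1st April 2006 and 31st March 2014" and sets the index date at 6 months post-partum. Model estimation specifies a Weibull accelerated failure time model for 5-year risk. The article states no run-off period, no earlier censoring date, no later data cut and no truncation of follow-up at 5 years.

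**The concern.** Back-dating a two-claim diagnosis to the first physician claim is sound only if the data run long enough past the end of follow-up for the second claim to be seen. Here the permitted wait is up to one year and the margin is zero. A first physician claim just before the cut has almost no chance of confirmation, and one made a year earlier has its full chance. The woman who is not confirmed is kept in the risk set to the end as event-free.

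The error runs one way: events are lost and none are gained. It depends on calendar date, so it falls on women still under observation in the last year, who are late in their own follow-up. A parametric model fitted to such data sees a late hazard that is too low, which pulls the Weibull shape down and carries into predicted risk. Bootstrap validation and calibration in Ontario use the same outcome dates and cannot reveal it.

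**Working it through.** No figure stated in the article bears directly on this point, so there is none to reproduce. The check is a calendar-time calculation.

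**Inputs from the article**
- Births from 1 April 2006 to 31 March 2014, so index dates run from about October 2006 to September 2014: 8 years, taken as uniform. With the first index date at time 0, the cut is at 12.5 years and the affected year runs from 11.5 to 12.5.
- Event rate from the Sample size section (a different cohort, used only for scale): 2294 / 756,956 = 3.03 per 1000 person-years, taken as constant (true shape 1).

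**Assumptions, not in the article**
- Share of events found only by two claims: 50–100%.
- Gap between claims: from a truncated exponential with a 2–3 month scale to uniform over 0–1 year.
- Exit through conception or death: 0–0.2 per year.

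**Step 1: who is exposed.** Within the 5-year horizon, only women with an index date after about 1 April 2013 are at risk in the affected year: 1.5 / 8 = 18.75%. No at-risk time in years 1–3 is affected, against 1.6% of year 4 and 11.1% of year 5.

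**Step 2: share of person-time, with no other exits.**
- Within 5 years: women indexed at 6.5–7.5 contribute 0.5 in total and those at 7.5–8 contribute 0.5, so (0.5 + 0.5) / 8 = 0.125 year per woman. Total time is 5 − 0.125 / 8 = 4.98. Share: 0.125 / 4.98 = 2.5%.
- All follow-up: the mean is (4.5 + 12.5) / 2 = 8.5 years. Share: 1 / 8.5 = 11.8%, or 11.6% after allowing for diabetes events.
- With exits at up to 0.2 per year, the shares fall to 1.6% and 5.6%.

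**Step 3: chance that a first physician claim in that year goes unconfirmed.** Averaged over the year this is 50% for a uniform gap. For an exponential gap with scale s, truncated at one year, it is s − e^(−1/s) / (1 − e^(−1/s)): 0.25 − 0.0183 / 0.9817 = 23% at 3 months, and about 16% at 2 months.

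**Step 4: events lost.**
- All follow-up, upper end: 11.6% × 50% × 100% = 5.8%. Lower end (exit 0.2, 2-month scale, half claims-only): about 0.4%.
- Within 5 years, upper end: women reach 5 years and leave as the cut approaches, so fewer are at risk when the miss probability is highest. With r years left to the cut, index dates spanning 0.5 + r years are still at risk and the miss probability is 1 − r. The loss is ∫₀¹ (0.5 + r)(1 − r) dr / 8 = 0.417 / 8 = 0.052, and 0.052 / 4.98 = 1.0%. Multiplying the averages (2.5% × 50% = 1.25%) slightly overstates it. Lower end: about 0.1%.

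**Step 5: effect on the model.** Weibull fits to the expected data under these ranges give:
- all follow-up used: shape 0.95–0.997 instead of 1, and 5-year risk about 0.3–3.2% too low (relative);
- times truncated at 5 years: 5-year risk about 0.1–1.1% too low (relative).

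In absolute terms, a constant rate of 3.03 per 1000 gives a 5-year risk of 1 − e^(−5 × 0.00303) = 1.50%. A 3.2% relative shortfall takes it to about 1.46%.

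**The case against.** The strongest objection is materiality. The target is 5-year risk, about 81% of women could complete that horizon before the affected year begins, and the loss within it is about 1% or less. The article already reports 90.0% sensitivity and an 82.6% positive predictive value for the outcome definition, so this shortfall is minor beside the misclassification it discloses. That stands as a reason to rate the point low. It does not remove it, because the loss depends on calendar date and comes from a date the plan can choose.

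The upper figures need every event to be claims-only, a uniform gap and no exits for conception or death. The article also does not say whether times are truncated at 5 years. Both limits stand, which is why ranges are given.

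The article describes data availability as current at the time of writing. A refresh, or database dates already confirmed with later claims, would remove the problem. The article states neither.

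Two stronger readings do not hold. A reader might infer that events are under-counted in every woman's last year of follow-up. Women who leave earlier through diabetes, death or conception are untouched by the data cut. A reader might also infer that recent births will look lower risk. Birth year is not among the predictors in Table 1, so the model estimates no such contrast.

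**Conclusion.** The point holds in a limited form, as a minor correction. As written, the end of data, the end of follow-up and the back-dated two-claim rule together under-count claims-based events with a first physician claim between 1 April 2018 and 31 March 2019, among women still followed then. This follows from dates and rules that the article fixes, so it is not detail left to a fuller document.

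The direction is certain unless the dates were confirmed with later data. The size depends on the assumed claims-only share, claim gap and exit rate, and on whether the Weibull fit uses all follow-up. On either basis it is too small to threaten the study, but it is avoidable.

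**What to change.** Any one of these resolves the point:

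- End follow-up on 31 March 2018 and use data to 31 March 2019 only to confirm second claims.
- Keep 31 March 2019 and draw an outcome extract that runs at least one year longer.
- If the database dates to 31 March 2019 were already confirmed with later claims, state this in the Outcome section.

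In each case, also state whether follow-up is truncated at 5 years for the Weibull fit, since that largely determines how much the cut matters.

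The earlier date has a cost. Potential person-time per woman within 5 years falls from 4.98 to 4.86 years (2.5%). Over all follow-up it falls from 8.5 to 7.5 years (about 12%). Hospital and drug events in that year, which are fully observed, are dropped too, as are claims events already confirmed. Women with a potential full 5 years fall from 7.5 / 8 = 93.75% to 6.5 / 8 = 81.25%, before other exits. Precision should remain ample: the Background describes over 200,000 deliveries, against a stated minimum of 6193 women. The longer extract avoids this loss but depends on newer data being available.

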### Main predictors

Table 1 lists the predictors and the pre-specified functional forms for each.

**Table 1 Tab1:** Pre-specification of predictors for risk prediction model

Variable type	Variable	Specification	df
Demographics	Age at index	Continuous variable	1
	Income quintile	Five categories	4
	Rurality	Binary: yes/no	1
	Immigrant status	Three categories (non-immigrant, previous (over 10 years ago), recent (10 years or less)	2
	Ethnicity	Three categories (South Asian, Chinese, Other)	2
Lifestyle	Pre-pregnancy BMI, kg/m^2^ (self-reported)	Continuous	1-3
Lifetime Health history	Previous mental health condition	Binary: yes/no	1
	Previous cardiovascular disease	Binary: yes/no	
Prior pregnancy history	Parity	Five categories (0, 1, 2, 3, > 3)	4
	Gravidity	Four categories (1, 2, 3, > 3)	3
	Previous GDM	Three categories: yes/no/NA	2
	Previous gestational hypertension or preeclampsia	Three categories: yes/no/NA	2
Index pregnancy	50 g oral glucose challenge test, mmol/L	Continuous	1-3
	GDM	Binary: yes/no	1
	Preeclampsia	Binary: yes/no	1
	Gestational hypertension	Binary: yes/no	1
	Caesarean-section	Three categories: planned/emergency/no	1
	Premature delivery	Binary: yes/no	1
Newborn	Birthweight	Continuous (for women with a multi-fetal birth, the child with the higher birthweight will be used)	1
	Large for gestational age (LGA) birthweight > 90th	Binary: yes/no (for women with a multi-fetal birth, any child with a record for LGA will be used)	1

Choice of the candidate predictors was informed by a systematic literature review, consultation with the project advisory board, clinicians, and the availability of the predictors within the study’s data sources. To enhance usability, predictors of the model were also chosen based on their likely availability to intended users of the model. Continuous variables with limited variation and binary variables with small counts will be excluded. While categorical variables have been pre-specified, frequency distributions will be examined and categories may be combined where there are small numbers. Interactions between all predictors and each of age, GDM and ethnicity will be considered for inclusion into the model due to expected differences in the effect of these predictors by the selected variables. Interactions which improve model fit will be included in the final model.

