### Sample size

For the period between 2014 and 2016, there were 231,618 women who delivered a baby and 756,956 person-years of follow-up. Overall, 2294 women developed incident type 2 DM during follow-up (unpublished data). Using the criteria specified by Riley et al. and the *pmsampsize* R package, we calculated the minimum sample size required to be 6193 women to minimize overfitting and ensure the estimation of precise model coefficients [35, 36].

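### The end-of-follow-up rule omits loss of OHIP coverage or departure from Ontario, which adds a downward bias of unknown size to the estimated 5-year risk

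*Protocol article*

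**What the plan says.** The Outcome section fixes follow-up with a closed list: women are "followed up from index date until the earliest of incident diabetes, death, new pregnancy conception date, or study end-date", the last being 31 March 2019. No other section adds a further end point.

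The outcome comes from the Ontario Diabetes Database, which according to Data sources "contains all individuals with DM in Ontario". On what feeds it, the same section says: "This database captures data from hospital discharge abstracts, Ontario drug benefit claims and physician service claims". The case definition in the Outcome section uses the same three kinds of record.

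Coverage is addressed once, before index. The Participants section removes women who were "ineligible for the Ontario Health Insurance Plan or were a non-Ontario resident in the 2 years prior to index date", and gives the reason: "since predictor and outcome data for these women will be incomplete". Index is 6 months after delivery.

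**The concern.** The protocol recognises that outcomes cannot be seen without coverage, but applies this only to the 2 years before index. Outcomes accrue after index, where the reasoning applies at least as strongly. A woman who moves away in year 2 can generally no longer generate an Ontario hospital, claims or drug record. Under the stated rule she still counts as at risk and event-free until the study end-date. Her later pregnancies would generally go unrecorded as well, so she is not censored at conception while women who stay are.

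The product is an absolute 5-year risk, intended for electronic records and a public calculator, so a shift in the baseline hazard reaches users directly. The planned internal checks share the flaw. Calibration-in-the-large compares mean predicted risk with a Kaplan-Meier risk built on the same follow-up times, and the bootstrap resamples the same data. Predicted and observed risk would be low together and appear to agree.

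Table 1 also contains predictors that could be related to moving, among them immigrant status with a category "recent (10 years or less" since arrival, ethnicity, rurality and income. If departure differs across their levels, the coefficients could be affected as well as the baseline.

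**Working it through.** The plan states no figure on this point, so there is nothing to reproduce. The direction follows from the text. The size can only be illustrated.

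**Inputs**

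- Event rate λ, from Sample size: "there were 231,618 women who delivered a baby and 756,956 person-years of follow-up", with 2294 incident cases. λ = 2294 / 756,956 = 0.00303 per year, or 3.03 per 1000 person-years. These are 2014 to 2016 deliveries, not the 2006 to 2014 derivation cohort, and their censoring rule is not given, so the rate is illustrative.
- Illustrative true 5-year risk: 1 − exp(−5 × 0.00303) = 1.504%.
- m, the annual rate of leaving Ontario or losing coverage: **assumed**, constant, 0.5% to 5%.
- c, the annual rate of censoring at a new conception among women still in Ontario: **assumed**, 0, 0.1 or 0.2.

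**Simple formula (c = 0).** The unobservable share of 5-year person-time, and so roughly the relative shortfall, is 1 − (1 − exp(−5m)) / (5m).

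- m = 1%: 1 − 0.04877/0.05 = 2.5%
- m = 2%: 1 − 0.09516/0.10 = 4.8%
- m = 5%: 1 − 0.22120/0.25 = 11.5%

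**With conception censoring.** Women still visible and at risk: I(t) = exp(−(λ + c + m)t). Women who have left but are still counted: L(t) = the integral from 0 to t of m·exp(−(λ + c + m)s) ds. The apparent hazard is λ·I(t) / (I(t) + L(t)). Integrating it over 5 years gives H, and the apparent risk is 1 − exp(−H).

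| m per year | Share leaving within 5 years, 1 − exp(−5m) | Apparent risk, c = 0 | c = 0.1 | c = 0.2 |
|---|---|---|---|---|
| 0.5% | 2.5% | 1.485% (−1.2%) | 1.482% (−1.5%) | 1.477% (−1.8%) |
| 1% | 4.9% | 1.467% (−2.5%) | 1.460% (−2.9%) | 1.452% (−3.5%) |
| 2% | 9.5% | 1.431% (−4.8%) | 1.419% (−5.7%) | 1.403% (−6.7%) |
| 3% | 13.9% | 1.397% (−7.1%) | 1.379% (−8.3%) | 1.357% (−9.8%) |
| 5% | 22.1% | 1.331% (−11.5%) | 1.304% (−13.3%) | 1.272% (−15.4%) |

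Brackets show the change relative to 1.504%. With c = 0 the integration agrees with the simple formula. The shortfall grows with c because women who stay leave the risk set at conception while those who have gone do not.

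**Absolute size.** With c = 0, the shift is 1.504 − 1.467 = 0.04 percentage points at m = 1%, and 1.504 − 1.431 = 0.07 at m = 2%.

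**Differential departure, purely hypothetical.** If one group left at 5% a year and its reference group at 1%, the hazard ratio would be multiplied by about 0.885/0.975 = 0.91, a downward bias of about 9%.

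**The case against.** Several objections carry weight.

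- *The rates are invented.* The article gives no out-migration or coverage-loss rate. At 1% to 2% a year the shift on a 1.5% risk is a few hundredths of a percentage point, and nothing in the article shows that this would alter ranking, discrimination or use of the tool. This stands.
- *Other errors pull the other way.* A reader might infer that the final 5-year risk will be too low. The article does not support that. Its stated sensitivity of 90.0% and positive predictive value of 82.6% imply recorded cases of 0.900/0.826 = 1.09 times true cases in the validation population, an over-count of about 9%. That figure need not carry over to incident cases in this cohort, but the net direction is open. Only a downward component is established.
- *Differential bias is not documented.* A reader might take it that the coefficients for immigrant status, ethnicity or rurality are distorted. No section says these groups leave at different rates, and the 2-year residence requirement already removes the newest arrivals and women with recent coverage gaps. The 9% figure shows what could happen, no more.
- *The arithmetic is not this design.* A fixed 5-year window with constant rates does not model follow-up that can run to about 12.5 years (index from October 2006, end March 2019). The figures are illustrations.
- *External validation might reveal it.* It might also be inferred that no calibration check could detect the problem. That is shown only for the internal checks. The External validation section allows for recalibration in Alberta, and it fixes no stop rule there, so no Alberta rule is wrong.
- *An article condenses.* A full plan may contain the missing date. However, an earliest-of list is a complete operational rule, and followed literally it keeps women who have left at risk. The point therefore remains a fair one.

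**Conclusion.** The omission is real and conflicts with the protocol's own reason for its pre-index exclusion. Applied as written, the rule counts time in which diabetes cannot be observed as event-free, which adds a downward bias to the estimated hazard and to the internal Kaplan-Meier risk. Internal calibration and the bootstrap would not reveal it.

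The size is unknown. Under an assumed constant loss of 1%, 2% or 5% a year, the relative shortfall over 5 years is about 2.5%, 4.8% or 11.5%, rising to 3.5%, 6.7% or 15.4% with an assumed conception-censoring rate of 0.2 a year. Distortion of individual coefficients is possible but depends on differences in departure that the article does not report. This is a modest flaw that is cheap to remove before analysis; it does not by itself undermine the study.

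**What to change.** In the Outcome section, add end of OHIP eligibility or of Ontario residence to the events that end follow-up. The eligibility and residence data are already used for the exclusions in the Participants section, so no new source is needed. When follow-up is defined for the Alberta cohort, use the matching end-of-coverage date; the External validation section already links the Alberta insurance registry. Aligned rules keep a difference in censoring from being mistaken for poor transportability.

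The change removes the bias provided that leaving is unrelated to diabetes risk given the predictors. It costs one extra date per woman and slightly less person-time.

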### Sample size

For the period between 2014 and 2016, there were 231,618 women who delivered a baby and 756,956 person-years of follow-up. Overall, 2294 women developed incident type 2 DM during follow-up (unpublished data). Using the criteria specified by Riley et al. and the *pmsampsize* R package, we calculated the minimum sample size required to be 6193 women to minimize overfitting and ensure the estimation of precise model coefficients [35, 36].

### Analysis plan

All data manipulations will be carried out using Wickham’s *tidyverse* package [37] and modelling will be conducted using Harrell’s *rms* package in R [38]. The TRIPOD statement was used to devise the analysis plan and will be used to guide the reporting of the development and validation of the proposed model [39].

### Data cleaning and coding of predictors

Continuous predictors will be assessed using descriptive summaries and histograms. Implausible values will be set to missing, and highly skewed predictors will be truncated at the 99.5 percentile. For example, if a woman has a pre-pregnancy BMI value of 51 kg/m^2^, which surpasses the calculated 99.5^th^ percentile BMI of 50 kg/m^2^, then her BMI will be assigned as 50 kg/m^2^. Continuous predictors will be centered on their mean values. Continuous variables will be included in the model as linear or non-linear terms using restricted cubic splines, depending on model fit. Knot placement in restricted cubic splines will be based on the percentile distribution of the continuous variable. The definitions of all variables have been pre-specified to minimize risk of over-fitting.

